In developing the evaluation of the Birthing in Our Community program we aimed to compare outcomes for mothers and infants with a similar cohort of women receiving standard care. After reviewing the statistics from across South East Queensland, the most appropriate comparison cohort was women attending the Royal Brisbane and Women’s Hospital (RBWH) where senior managers and researchers agreed to collaborate on a joint project and funding submission. However, as the funding was being awarded, the RBWH also changed their model of care (2013) for Aboriginal and Torres Strait Islander women through the Ngarrama Indigenous Maternity Service and it is no longer standard care. The Ngarrama Service is a government-funded midwifery continuity of care service for women having an Aboriginal and/or Torres Strait Islander baby/ies and planning to birth at the RBWH (located fewer than six kilometres north of the MMH). Thus we have agreed to evaluate both new services, Birthing in Our Community and the Ngarrama Service, and will compare them to each other, and to women receiving standard care and to baseline data from both hospitals. (Note: not all women having Aboriginal and Torres Strait Islander babies at both MMH and RBWH access the Indigenous-specific models of care hence the concurrent comparison with standard care). Table 2 outlines the components of the different models of care available to women having Aboriginal and Torres Strait Islander babies at the MMH and RBWH. For the first time, researchers will test the effectiveness of caseload midwifery in an urban setting where 100% of the midwives’ caseload are women having Aboriginal and Torres Strait Islander babies receiving care across the maternity continuum (antenatal, birth, until 6 weeks postnatal).

**Table 2 Tab2:** Models of care available to Aboriginal and Torres Strait Islander families at study sites

Birthing in Our Community (Group 1)	Standard Care (Groups 2, 5)	Ngarrama Maternity Service (Group 4)

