#### Power and sample size

This study has been powered to detect changes in clinical outcomes and the number of women accessing care per annum in each program [33]. During the 3.5-year recruitment period, we will aim to access routinely collected data for approximately 420 women at MMH, and 350 from RBWH (based on an estimated 20% attrition rate). The change in outcomes has been estimated based on changes seen in the Townsville Mums and Bubs program that reported a reduction in preterm birth [34] (Table 4).

**Table 4 Tab4:** Power calculations with *n* = 350 in each arm + 20% for attrition

Outcome	From %	To %	No./ cohort	Power
Proportion of women who attend ≥ 5 antenatal visits	81.0	90.0	261	0.924
Proportion of women who were smoking after 20 weeks	42.0	31.0	318	0.858
Preterm birth < 37 weeks pregnancy	16.0	9.0	350	0.801
Exclusive Breast feeding at discharge (2007–09 Mater data)	78.0	88.0	240	0.942

The sample size for the ethnographic component of the study (‘Tell My Story’) will involve a smaller group of women from each cohort. The project aims to recruit up to 25 women from each cohort, which factors in a 20% attrition rate (25*.8 = 20).

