### Data analysis and management

#### Quantitative

Clinical data will initially be collected in a re­identifiable form (via the unique patient identifier) so that it can be linked with data obtained from other sources (e.g. surveys), to enable the economic analyses to be undertaken. Once merged, identifiers will be removed and only the coded number will remain.

Quantitative analyses will compare the difference in clinical outcomes between Birthing in Our Community (intervention), the Ngarrama Service (concurrent control), standard care (historical and concurrent control), and also non-Indigenous women and babies (historical and concurrent control) at MMH and RBWH.

Data on all women attending either hospital during the study period will be extracted. Women transferring in from other hospital or rural and remote areas for higher-level services (variable available), and those with no antenatal care will be excluded from analysis. Analyses will be by birth model of care and women with multiple births and their infants with identified fetal anomaly will be excluded from analysis unless noted otherwise.

Initial bivariate analysis will investigate possible differences between the cohorts for baseline socio-demographic (socio-economic status), and clinical characteristics (e.g. age, parity, body mass index, smoking, obstetric history) that could affect outcome measures. Dependent on data type, analysis will be undertaken using an independent samples t-test, Mann-Whitney U test or chi-squared test. Outcome measures will be presented using relative risks with 95% confidence intervals. Multivariate logistic, linear regression models and propensity score matching will be used to adjust for confounders. Longitudinal outcomes (e.g. breastfeeding) will be analysed with generalized estimating equations to account for the correlation between observations repeated in the same person. To understand the mechanism or process that underlies the effect of model of care on outcomes, mediation analysis will be conducted to identify if and to what extent the other variables explains the relationship. All withdrawals, losses to follow-up, and deaths will be reported. Analysis will be performed with SPSS Version 22.0/Stata 14.0 and statistical significance will be at the 0.05 level.

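### Table 4's power uses a programme-versus-no-programme effect and is tied to no named contrast; for Birthing in Our Community versus Ngarrama it is overstated if Ngarrama has any material benefit

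*Protocol article*

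**What the plan says.** **Power and sample size.** The section speaks of changes in outcomes and of the women accessing each programme. It expects routine data on about 420 women at MMH and 350 at RBWH over a 3.5-year recruitment period. Table 4 is headed "Power calculations with *n* = 350 in each arm + 20% for attrition", and its preterm row reads "Preterm birth < 37 weeks pregnancy 16.0 9.0 350 0.801". On the source of the effects it says: "The change in outcomes has been estimated based on changes seen in the Townsville Mums and Bubs program". The breastfeeding row labels its starting rate as Mater data from 2007–09, before BiOC was launched in 2013.

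**Study setting.** RBWH was selected as the standard-care comparison, but in 2013 it changed its model of care "through the Ngarrama Indigenous Maternity Service and it is no longer standard care". The plan became to compare the two new services with each other, with women receiving standard care, and with baseline data from both hospitals. Table 2 describes Ngarrama as a hospital-based midwifery group practice.

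**Data analysis, Quantitative.** The comparators listed for BiOC include "the Ngarrama Service (concurrent control", alongside historical and concurrent standard care and non-Indigenous women. The threshold is given as "statistical significance will be at the 0.05 level".

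**Background, Caseload midwifery models.** Midwifery group practice is credited with reducing preterm birth and increasing breastfeeding.

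**Discussion.** The study is said to have the power to detect a difference in preterm birth. No contrast is named.

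**The concern.** The comparator changed and the power section does not reflect it. The From and To rates describe what happens when a programme is introduced. The only sample sizes printed beside them belong to two hospitals, each of which now runs a new midwifery service. For 16% versus 9% to be the expected gap between those services, Ngarrama would have to leave preterm birth where it was. The Background gives reason to expect otherwise.

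The risk lies in interpretation. If BiOC and Ngarrama do not differ significantly on preterm birth, a reader relying on Table 4 and the Discussion could take this as an adequately powered finding that the services perform alike, when the study may have had little chance of separating them. The result is meant to inform wider implementation, so the reader needs to know which comparisons the study can resolve.

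**Working it through.** **Inputs.** From Table 4: rates 16% and 9%, 350 per arm. From the Quantitative section: significance level 0.05. Two-sided testing is assumed because the article does not say; it reproduces the table.

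**Formula** (two-proportion z-test, equal arms, no continuity correction), with p̄ the mean of p1 and p2:

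- S0 = √[2·p̄(1−p̄)/n]
- S1 = √[(p1(1−p1) + p2(1−p2))/n]
- power = Φ[(|p1−p2| − 1.96·S0)/S1]

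**Step 1: reproduce the article's figure.** For 16% v 9%, n = 350: p̄ = 0.125, S0 = 0.0250, S1 = 0.0249. Then (0.07 − 0.0490)/0.0249 = 0.845 and Φ = 0.801, as printed. The other three rows also reproduce at 350 per arm: antenatal visits 0.924, smoking 0.858, breastfeeding 0.942. The arithmetic is sound; the question is which contrast it describes.

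**Step 2: preterm birth, BiOC versus Ngarrama.** Hold BiOC at 9% and let Ngarrama deliver part of the 7-point reduction. The Ngarrama rates are assumptions.

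| Ngarrama rate | Share of the 7-point effect | (difference − 1.96·S0)/S1 | Power, 350 per arm | Power, 420 v 350 | n per arm for 0.80 |
|---|---|---|---|---|---|
| 16% | 0% | 0.845 | 0.80 | 0.84 | 350 |
| 14.25% | 25% | (0.0525 − 0.0475)/0.0242 = 0.21 | 0.58 | 0.63 | 584 |
| 12.5% | 50% | (0.035 − 0.0459)/0.0234 = −0.47 | 0.32 | 0.35 | 1229 |
| 11% | 5/7 = 71% | (0.02 − 0.0445)/0.0227 = −1.08 | 0.14 | 0.15 | 3531 |

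If the two rates were equal there would be no difference to detect, so that case has no power figure. Using 420 v 350 changes little: at a Ngarrama rate of 15% power is 0.73.

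**Step 3: the other primary outcomes,** with Ngarrama at half of each Table 4 effect and 350 per arm:

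- antenatal visits, 85.5% v 90%: 0.44
- smoking after 20 weeks, 36.5% v 31%: 0.34
- exclusive breastfeeding at discharge, 83% v 88%: 0.47

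**Step 4: programme versus standard care or baseline.** A 16% to 9% change is the right kind of effect here. Power also needs the numbers in Groups 1, 2, 4 and 5 and in the 2009–2013 baseline. The article gives none of these, only totals by hospital, so no power can be computed for these contrasts without assumed counts.

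**The case against.** The strongest reply is that nowhere does the article say Table 4 is about BiOC versus Ngarrama. The From/To layout, the talk of changes and the 2007–09 starting rate fit a programme-versus-baseline or programme-versus-standard-care reading, and both contrasts are planned. This stands. The reading of Table 4 is an inference, and it would be wrong to say that the study lacks power for every contrast. What the reply does not supply is a sample size: 350 per arm is matched in the text only by the hospital totals, and the Discussion's claim names no contrast at all.

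A reader might go further in three ways that the documents do not support.

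- **Splitting the 420 MMH women between BiOC and standard care, and taking the resulting lower power as a ceiling.** The split is not in the article. Routine data run from late 2013 to 2019, longer than the 3.5-year recruitment period, and are to be extracted for all women attending either hospital. The available numbers may well be larger.
- **Inferring a high false-positive rate from four primary outcomes tested at 0.05 against several comparators.** Any such calculation needs independent tests, whereas these share women and comparison groups. The order of testing is also commonly left to an analysis plan, which is not shown.
- **Objecting that each service exists at only one hospital, so that model and hospital cannot be separated.** This is true of a direct service-to-service comparison, but the design includes concurrent standard care and baseline data at both hospitals, and adjustment is planned.

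**Conclusion.** The point holds in a limited form. Table 4 is arithmetically correct for a programme-versus-no-programme difference at 350 per arm, but the article does not say which planned contrast has that effect and those numbers. For BiOC versus Ngarrama the stated 0.801 applies only if Ngarrama has no effect on preterm birth. At 350 per arm any benefit lowers it: to about 0.58 at a quarter of the effect, 0.32 at half and 0.14 at a Ngarrama rate of 11%. The direction follows from the article's own account of midwifery group practice. The size depends on the assumed Ngarrama rates and on BiOC reaching 9%. For programme versus standard care or baseline the power is unknown rather than shown to be low. The Discussion's unqualified claim is therefore not supported as written.

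**What to change.** 1. In Power and sample size, state which contrast Table 4 refers to.
2. Give power separately for (a) each programme versus concurrent standard care and versus baseline, using the counts expected in each group over the routine-data window, and (b) BiOC versus Ngarrama, over a stated range of Ngarrama rates.
3. State that, at the current numbers and with BiOC at 9%, BiOC versus Ngarrama does not have power of 0.80 unless Ngarrama has essentially no effect, so that a non-significant result there is not evidence that the services are equivalent.
4. Qualify the power sentence in the Discussion by naming the contrast to which it applies.

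The cost is some wording, a recomputed table and an estimate of the group counts. The drawback is a less favourable power statement. The choice of primary contrast, and any testing order across the four outcomes, remain matters for the investigators and the analysis plan; this point does not require either to change.

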### Participant recruitment and informed consent

Written informed consent to participate in the study will be obtained from all participants. The privacy, wellbeing and safety of all participants is a paramount consideration, and will be ensured by strict adherence to eligibility criteria, ensuring the relevant Participant Information and Consent Form has been read and understood, and reminding participants of their right to withdraw from the study at any time, without penalty. Study data collection will not commence until the requisite site-specific Human Research Ethics Committee and Research Governance approvals have been secured.

#### Women’s surveys and Infant Assessments (Groups 1, 2, 4, 5)

Written information about the study will be provided to all women at both sites when they book into the hospital. Recruiting staff (midwives, health workers, and liaison officers) will fill out an ‘Expression of Interest’ referral form with women interested and willing for IBUS research staff to contact her to tell her more about the study. Women will then be contacted by IBUS research staff who will explain the study in more detail and invite them to participate. Women who agree to participate will be given, mailed or emailed the Participant Information and Consent Form, with verbal information provided by the research staff. Written informed consent to participate will be obtained by member/s of the research team who will meet women at their next antenatal visit or to ring them to discuss the study in more detail.

In line with the NHMRC *Values and Ethics Guidelines for Ethical conduct in Aboriginal and Torres Strait Islander Health Research* [32], women will be reminded that they may defer making a decision until they have had time to discuss the information with any “interested parties … formally constituted bodies … collectives or community elders” (p.14). Provision will also be made for answering any outstanding questions. Consent to participate will be obtained by member/s of the research team who will offer to meet them at their next antenatal visit or to ring them to discuss the study in more detail.

Although this study is not specifically targeting young women, we are guided by the National Statement in that they will not be excluded on the basis of age alone [35]. The study will also be guided by usual practice employed for clinical procedures whereby the best interests of the young woman, and her capacity to consent, will be assessed on an individual basis. Hence, young women “who are mature enough to understand and consent, and are not vulnerable through immaturity in ways that warrant additional consent from a parent or guardian” (p. 65) will be invited to consent in their own right [35]. Where there is any concern that immaturity renders a young woman vulnerable, she will not be invited to participate.

#### Routinely collected data (Groups 1–6)

We are seeking a waiver of consent to access routinely collected data for the all cohorts of women in order to satisfactorily answer the outcome measures. This will include both clinical and costing data. For women who participate in the IBUS surveys, consent will be sought to link IBUS survey data to routinely collected data. Initially the data will be collected in an identifiable form so we can be assured that data from different sources can be merged with each participant given one unique identifier. Once this is completed all identifiable data (e.g. name, address) will be removed and kept only in the participant log, which will be used to contact participants at different time points.

#### Tell My Story (Groups 1 & 4)

A smaller group of women will be invited to participate in the Tell My Story qualitative component. Women in the IBUS study who are interested in participating in further qualitative antenatal and postnatal follow-up will be approached by the IBUS research team.

#### Staff interviews and focus groups (Groups 1 & 4)

All staff members involved in planning or providing specialized maternity care to women having Aboriginal and/or Torres Strait Islander babies at MMH or RBWH will be eligible to participate in these individual and focus groups interviews. Staff will be invited to participate by the IBUS research team. A researcher will explain the staff interview process to the staff either face-to-face or on the phone using the Participant Information and Consent Form for Staff which will be emailed in advance. Staff who provide written consent to participate will be interviewed either annually or when exiting a role. Interviews will be conducted one-on-one or in small focus groups. Interview participants will be reimbursed for parking costs and given a small gift (e.g. chocolates) as a show of thanks and appreciation for their time.

#### Staff quantitative surveys (Groups 1–6)

Staff will be invited to complete surveys on their experiences of working in the different models of care. The initial invitation to participate will be sent to staff via email with the option for them to complete electronic surveys via an email link or paper surveys distributed via team leaders from the research team. Staff will receive face-to-face, text and email reminders to complete the survey.

### Data collection

#### Routinely collected clinical and costing data

Data for each mother/infant dyad at the MMH will be collected from several sources. MMH obstetric (MatriX), neonatal database and expenditure data (Australian activity based funding Diagnosis Related Groups [DRG] codes) will provide detailed patient-level information on inpatient contacts for the mother and baby. Routinely collected data including expenditure data will be collected from the RBWH where it will be coded before being merged with the study database. Perinatal data will also be extracted from the Queensland Health database.

The IUIH (MMeX) and ATSICHS (Medical Director and Pracsoft; MMeX) routinely collect data on service delivery (access, clinical data, e.g. immunisations, and expenditure data) which will also be collected. The clinical and costing outcomes data will be derived from routinely collected information and survey data.

#### Women’s surveys and infant assessments

Survey data collected at different time points will be used to measure program acceptability, sustainability and effectiveness; and infant growth and development. Women will be invited to complete face-to-face, postal or online surveys (their choice) at booking-in, 36 weeks of pregnancy, at two months and six months after birth. Maternal surveys will include questions related to women’s maternity care experience and out-of-pocket costs incurred in accessing maternity or child health services (see Table 5 for list of survey items). At two and six months after the birth, women will be asked to provide information about their infant’s development (Ages and Stages Questionnaire [36]). At six months postnatal, women and infants will be invited to participate in a face-to-face developmental assessment, and offered a developmental report on their infant’s performance on the Bayley-III Scales of Infant and Toddler Development [37]. Referral to a specialist will be available for infants identified with developmental delays or who otherwise raise concerns. Additionally, if any woman is identified to be at risk of depression or psychological distress or self-harm, she will also be offered referral to appropriate services.

**Table 5 Tab5:** Items included in Women’s antenatal and postnatal surveys

Items	Women’s surveys			
	1	2	3	4
Socio-demographic characteristics				
Indigenous status, maternal and paternal	✓			
Maternal relationship status	✓			
Educational attainment, maternal and paternal	✓			
Employment status, maternal and paternal	✓			
Government pension main source of income	✓		✓	✓
Has healthcare concession card	✓			
Has private health insurance	✓			
Has access to vehicle/transport	✓			
Number of places of residence during pregnancy		✓		
Current housing	✓	✓		
Experienced homelessness during pregnancy		✓		
Financial insecurity	✓	✓	✓	✓
Self-reported health problems				
Experienced health problems, mother and infant			✓	✓
Baby admitted to hospital, date, reason, duration			✓	✓
Mother admitted to hospital, date, reason, duration			✓	✓
Number of visits with baby to child health nurse, reason			✓	✓
Number of visit with baby to paediatrician & reason			✓	✓
Pregnancy, birth/labour & care				
Gestation/age of baby	✓	✓	✓	✓
General feelings about pregnancy	✓	✓	✓	✓
Number of weeks first contact with care for pregnancy	✓			
Where was care received	✓			
Plans for birth location	✓			
Experience of staff behaviour		✓	✓	
Culturally safe aspects of care (importance, satisfaction)	✓		✓	
Felt respected & understood by hospital staff (by area)			✓	
Felt treated poorly or judged by staff			✓	
Satisfaction with care, recommend to others		✓		
Known midwife present during labour/birth			✓	
Attendance of group antenatal classes		✓		
Smoking				
Current smoking status, including number of cigarettes per day	D	✓	✓	✓
Attempts to quit	D	✓		
Advised to quit by health staff		✓		
Smoking support received, perceptions		✓		
Smoking household members	✓	✓		✓
Feeding baby				
Previous breastfeeding experiences, inc. difficulties	D	✓		
Intentions to breastfeed, inc. duration	D	✓		
Confidence to breastfeed		✓		
Experience of breastfeeding, inc. initiation			✓	
Use of formula, inc. reasons, age of baby			✓	
What baby has been fed in past 24h			✓	✓
Where received feeding information			✓	
Use of commercial baby food				✓
Reasons for starting solids				✓
Partner involvement				
Partner’s feelings about pregnancy	✓			
Baby’s father & father figures (involvement, attended visits, support services)				✓
Social and emotional wellbeing				
Negative life events - full extended version	✓	✓		✓
Additional worries experienced	✓	✓		✓
Family separations			✓	
Positive wellbeing scale	✓	✓	✓	✓
Modified Kessler Psychological Distress Scale (K5)	✓	✓	✓	✓
Edinburgh Postnatal Depression Scale	D			✓
Practical Social Support Scale	✓			
Social support available, inc. partner		✓		
Out-of-pocket costs				
Time spent, support person, carer, transport, food & drink		✓		
All services accessed for pregnancy/birth/baby, number of visits, out of pocket cost per visit (i.e. not refunded by Medicare)			✓	
Out of pocket cost of medicines during pregnancy/birth/baby			✓	
Infant development				
Ages and Stages Questionnaire			✓	✓
Bayley III Cognitive, Language and Motor Skills (face-to-face assessment)				✓

Note: D = clinical data available

Participants will be provided with an AU$10 gift card after completing the booking-in and 36 weeks antenatal surveys and a large tote bag at 36 weeks. An AU$30 gift card and a small toy or bib/blanket will be given for the two and six-month postnatal surveys to thank women for their time. Women who participate with their infant in the Bayley assessment will receive an additional AU$10 gift card upon completion.

